### Analysis

Incorporation of a term for calendar time into our models for primary and secondary outcomes will allow us to control for secular trend. This strengthens the analysis by eliminating temporal improvements in clinical care processes that are unrelated to the intervention. Time to event analyses will use Cox proportional hazards models. For binary outcomes including loss to follow-up and completion of treatment steps such as post-treatment radiation within 6 weeks, logistic regression will be used. Intervention effect estimates will be adjusted for potential confounders including patient demographics, substance use, housing status, and cancer stage.

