### Chart review

Chart review will be conducted for all patients in the Otolaryngology-Head and Neck Surgery Clinic undergoing diagnostic workup, treatment, or post-treatment monitoring for head and neck cancer for the 2-year period leading up to implementation of the tool and the 2-year period after the tool has been implemented (with the 6 months prior to tool implementation excluded to avoid misclassification of exposure to the intervention, as discussed below). All patients with confirmed diagnosis of head and neck cancer who were seen in the clinic at least once will be included in the chart review. Based on prior clinic chart review, there are about 75 patients with head and neck cancer seen in the clinic each year who meet enrollment criteria. Thus, the chosen 4-year time period was selected to allow for inclusion of approximately 300 patients in our sample. Data will be extracted from patient charts and will include patient demographic factors, details of the diagnosis, and key treatment dates (Table 1). Unless noted, all clinical data will be collected from the medical record for both the intervention and control time periods, to minimize differential data collection methods that may influence comparisons.

**Table 1 Tab1:** Data elements collected in chart review

Phase/data type	Data element
General: demographics	Gender
	Race/ethnicity
	Primary language
	Insurance status
General: social characteristics	Smoking status
	History of alcohol use
	History of other substance abuse
	History of homelessness/being marginally housed
	Comorbidities
	History of HIV/AIDS
General: utilization	Otolaryngology-Head and Neck Surgery visit dates and status (attended/canceled/no-show/scheduled)
	Medical oncology visit dates and status (attended/canceled/no-show/scheduled)
	Radiation oncology visit dates and status (attended/canceled/no-show/scheduled)
	Patient only seen for hospitalization
	Most recent visit date
General: outcomes	Overall follow-up time
	Survival
General: results	Imaging for cancer monitoring
	All imaging
	Thyroid-stimulating hormone test dates and results
	All lab test dates and results
	Pathology dates and results
1. Workup and treatment planning	Date of diagnosis
	Date of referral to tumor board
	Date of presentation at tumor board
	Date imaging appointments sent, scheduled, and completed
	Date referrals sent, scheduled, and completed
	TNM staging
	Site
	Histology
	P16 test results*
	Treatment plan
	Dates of patient outreach^†^

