### Outcomes

Patients included in the study will be divided into two separate cohorts. The pre-treatment cohort will include patients with a confirmed diagnosis of head and neck cancer but who have not yet initiated treatment. The post-treatment cohort will include patients who have initiated treatment and are undergoing additional treatment modalities and monitoring. Patients who received a diagnosis of head and neck cancer and initiated any treatment will thus be present in both cohorts. Outcomes for each cohort consist of completion of key steps in the evaluation and treatment process, and are summarized in Table 2. Usual clinic protocols will be employed to address patients who are lost to follow-up (three outreach attempts, then moved to lost to follow-up list). Patients who are lost to follow-up will be included in the final analysis and will be considered to have not met the process outcome for their given cohort (i.e., it will be assumed that patients lost to follow-up from the pre-treatment cohort never initiated treatment).

**Table 2 Tab2:** Primary and secondary outcomes for each patient cohort

Cohort	Primary outcome	Secondary outcomes
Pre-treatment cohort: workup and treatment planning	- Time from diagnosis to initiation of treatment	- Time from diagnosis to presentation to tumor board - Time from diagnosis to dental evaluation - Time to first visit in medical oncology and radiation oncology clinics - Lost to follow-up (no visit for ≥ 6 months)
Post-treatment cohort: treatment	- Completion of tumor board treatment recommendations	- Lost to follow-up (no visit for ≥ 6 months) - Proportion of patients completing post-treatment radiation within 6 weeks (guideline-based treatment quality of care metric) [5, 6]

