### Classification of exposure to the intervention

Patients will be considered unexposed to the intervention if they entered one of the cohorts at least six months prior to implementation of the health IT tool intervention. Patients who entered a cohort less than 6 months prior to implementation of the intervention will be excluded from that cohort. All patients entering a cohort after implementation of the tool will be considered exposed to the intervention for that cohort. For example, if a patient was diagnosed with head and neck cancer 3 months prior to implementation of the intervention and initiated treatment 1 week after implementation of the intervention, they would be excluded from the pre-treatment cohort and would be included in the post-treatment cohort and considered exposed to the intervention.

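### Completion of treatment recommendations and loss to follow-up have no time horizon, yet go to logistic regression with a linear trend; if charts close with the 2-year post-period, the model can show a tool effect that does not exist

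*Protocol article*

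**What the plan says.** **Window (Chart review).** Charts are reviewed "for the 2-year period leading up to implementation of the tool and the 2-year period after the tool has been implemented". One stretch just before the start is left out, which the article describes as follows: "with the 6 months prior to tool implementation excluded to avoid misclassification of exposure to the intervention". Accrual is given as "there are about 75 patients with head and neck cancer seen in the clinic each year who meet enrollment criteria". The length of the window is derived from that rate: "the chosen 4-year time period was selected to allow for inclusion of approximately 300 patients in our sample". No date is given on which outcome observation closes.

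**Exposure (Classification of exposure to the intervention).** "All patients entering a cohort after implementation of the tool will be considered exposed to the intervention for that cohort". No minimum follow-up is attached.

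**Outcomes (Table 2).** The post-treatment primary outcome is "Completion of tumor board treatment recommendations", with no time limit. A secondary outcome in both cohorts is "Lost to follow-up (no visit for ≥ 6 months", with no window from entry. The radiation outcome in the same table does have its own 6-week limit. Patients lost to follow-up are scored as not having met the process outcome; patients still in treatment when charts close are not mentioned.

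**Model (Analysis; Minimum detectable effects).** "For binary outcomes including loss to follow-up and completion of treatment steps such as post-treatment radiation within 6 weeks, logistic regression will be used". All models carry a calendar-time term, which the section on detectable effects describes as linear. Cox regression is reserved for the time-to-event outcomes.

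**The concern.** Logistic regression has no censoring, so a patient who has not yet had time to complete is counted like one who never will. If observation closes with the post-period, time available depends only on entry date. It is therefore entangled with both the exposure indicator and the calendar term, and every patient with short follow-up is exposed.

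The trend term does not repair this. The shortfall is not linear in entry date: it is negligible for most entrants and severe for the last few months. A single straight slope, fitted across both periods, is dragged down by those last entrants. Carried across the whole window, it predicts a larger fall between the periods than was observed, and the exposure term makes up the difference. For completion, that difference reads as a benefit of the tool.

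At stake are the post-treatment primary outcome and, to a lesser extent, loss to follow-up. The Discussion says that the results will inform a multi-center trial.

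**Working it through.** **1. Inputs.** From the article: 24 months before and 24 months after implementation, the 6 months before implementation excluded, about 75 patients a year, two-sided alpha 0.05, linear trend. Assumed, because the article gives no figures: time to completion, eventual completion, and rate of loss.

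**2. The plan's own figures.** These show which model is meant: an exposure step plus linear entry date. For contiguous 24+24 months, between-period variance is 12² = 144 and within-period variance 24²/12 = 48. So R² = 144/192 = 0.75 and the variance inflation is 1/(1 − 0.75) = 4.
- Cox: events = (1.96 + 0.84)² × 4 / (0.25 × ln(2.25)²) = 7.85 × 4 / (0.25 × 0.658) = 191 for a hazard ratio of 2.25.
- Logistic: OR = exp{2.80 × √[4 / (n × 0.25 × π(1 − π))]}. With n = 300 and π = 0.5 this is exp(2.80 × 0.462) = 3.65. With n = 200 and π = 0.2 it is exp(2.80 × 0.707) = 7.25. The article states 3.4 to 6.7.

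The order of magnitude agrees. Exact reproduction is not possible, because the event fraction and the confounder correlation are not given.

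**3. Time available if observation closes at month +24.**
- Layout A (the 6-month gap lies inside the 48 months; 75 × 3.5 = 262 patients): unexposed 30–48 months, exposed 0–24.
- Layout B (the gap is added to the 48 months; 75 × 4 = 300 patients): unexposed 30–54 months, exposed 0–24.

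In both, 6/24 = 25% of exposed patients have less than 6 months and cannot show a 6-month gap.

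**4. The mechanism in one worked case.** Suppose there is no tool effect and no secular trend, 80% complete eventually, and completion takes 1 month plus an exponential delay with median 3 months. With f months available (f > 1), the probability of observed completion is 0.8 × (1 − 2^(−(f−1)/3)):

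| Months available | 24 | 12 | 6 | 3 | 1 |
|---|---|---|---|---|---|
| Observed completion | 0.80 | 0.74 | 0.55 | 0.30 | 0 |

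The exposed average is (0.8/24) × [23 − (3/ln 2)(1 − 2^(−23/3))] = (0.8/24) × (23 − 4.31) = 0.62. The unexposed value is 0.80. The crude OR is (0.623/0.377)/(0.8/0.2) = 0.41. With the linear entry-date term the direction reverses: the median simulated OR is 6.0 in layout A (74% of trials significant) and 3.7 to 3.8 in layout B (53–55%).

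**5. Range for completion.** No true effect; lognormal course with median 2 to 4.8 months. False benefit means a significant result favouring the tool, nominally 2.5%.

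| Setting | Adjusted OR | False benefit |
|---|---|---|
| 80% completion, layout A, n = 262 | 3.8–9.0 | 44–90% |
| 80% completion, layout B, n = 300 | 2.6–4.9 | 27–74% |
| 35–50% completion, both layouts | 1.4–3.2 | 9–49% |
| 80%, layout A, +3 months after last entry | 1.1–3.3 | 5–42% |
| 80%, layout A, +6 months | 1.0–1.6 | 2–9% |
| 80%, layout A, +12 months | about 1.0 | 2–3% |

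With the lagged exponential course instead (70–80% completion, median 3–4 months after a 1–2 month lag), 6 extra months leave an OR of 1.5–1.8 and 12 extra months 1.1–1.25.

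**6. Loss to follow-up.** No true effect, closure at month +24; an OR above 1 means more loss with the tool. A constant loss rate of 10–30% per year gives an adjusted OR of 0.8–2.1 with 6–19% two-sided rejection. Early, front-loaded loss (25–50% eventually) gives 1.6–3.3 with 12–43%. Longer observation helps less here: at 30% per year in layout A the OR is 2.06, then 1.85 with 6 extra months and 1.42 with 12.

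**7. The remedies under the same null.** Cox regression with the same calendar term, censored at closure: median hazard ratio 0.96–1.02, rejection 4–6%. A fixed 12-month window with full follow-up: median OR 0.87–1.08, rejection 3–6%.

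**The case against.** The strongest reply is that closure at month +24 is inferred. Chart review names the periods whose patients are reviewed and gives no abstraction date; Table 1 collects overall follow-up time, survival and most recent visit. A condensed article may leave the cutoff, and the scoring of patients still in treatment, to a fuller document. This stands as a limit on size: about 12 months of observation after the last entry would largely remove the completion bias. It does not remove the point, because the article commits to no such period and sends outcomes without a horizon to a model that cannot censor.

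A second reply concerns inputs. The detectable-effect section plans on outcome prevalence of 20–50%, not 80%, and on analyses of 200–300 patients. That also stands, and the lower range of 1.4–3.2 belongs beside the higher one.

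A third is that this is a pilot. Effect estimation is declared secondary, and proceeding to the main trial depends only on tool use (80% of sessions and 80% of eligible patients). A biased odds ratio would not drive that decision. This lowers the priority.

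A reader might also infer that all the binary outcomes are biased strongly in the tool's favour. They are not. Loss to follow-up mostly moves towards apparent harm; in the pre-treatment cohort, risk arguably ends at treatment start, so the constant-rate model fits it poorly. Radiation within 6 weeks has its own window.

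Nor does the article say that deaths count as loss. Read literally, the definition would include them, but Outcomes also describes an operational route (three outreach attempts, then a list), and survival is abstracted. This calls for a clarifying sentence; it is not a demonstrated bias.

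**Conclusion.** The point holds as a conditional one and should be fixed. The stated method is unsuitable for two outcomes without a time horizon when follow-up depends on entry date. If observation ends with the 2-year post-period, a tool with no effect gives an adjusted odds ratio for completion of about 1.4 to 9.0, depending on completion rate, layout and course length. The upper part of that range exceeds the effects that the study is sized to detect (3.4 to 6.7).

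The size rests on assumed completion times and rates and on the inferred closure date. It would be wrong to quote the upper figures alone, or to treat closure at month +24 as a stated fact. For loss to follow-up the adjusted bias is smaller under a constant rate, larger if loss is early, and mostly unfavourable to the tool. Because feasibility decides whether the main trial proceeds, this is a correction to make before analysis and not a bar to the pilot.

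**What to change.** State a chart-closure date for outcomes, then adopt one of two analyses for completion and loss to follow-up.

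- **Preferred:** the Cox model already planned, with time from cohort entry, censored at closure. To keep the rule that lost patients count as not completing, leave them at risk of completion until closure. Date loss to follow-up at the point where the 6-month gap is complete. This drops nobody and costs only analysis wording.
- **Alternative:** logistic regression on a fixed window from entry (for example 12 months), including only patients whose whole window falls before closure. This drops late exposed entrants unless abstraction runs longer by the length of the window.

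Add one sentence saying that known deaths are not counted as loss to follow-up. Survival is already collected, so no new data are needed. The 6-week radiation outcome can stay as it is.

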### Minimum detectable effects

In Cox models for time to event, the sample of 300 will provide 80% power within two-sided tests with alpha of 0.05 to detect a hazard ratio of 2.25 for the effect of the intervention, after adjusting for a linear temporal trend as well as confounders. Estimation of preliminary effects should be considered secondary objectives. The sample size we propose is based on feasibility outcomes, and therefore the simulations below demonstrate that the pilot sample size would only detect a substantial effect size. Depending on the feasibility outcomes, we would proceed to a larger trials with the ability to detect more modest effects. With the present number of patients, in Cox models for time to event, the sample of 300 will provide 80% power within two-sided tests with alpha of 0.05 to detect a hazard ratio of 2.25 for the effect of the intervention, after adjusting for a linear temporal trend as well as confounders. For binary outcomes including loss to follow-up and completion of stages, it will provide 80% power to detect intervention odds ratios of 3.4 to 6.7, depending on the number of patients included in the analysis (200–300) and the prevalence of the outcome (20 to 50%), again after adjusting for a linear temporal trend and confounders. These estimates were obtained using simulations implemented in R Version 3.4.3.

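### The lower end of the detectable odds ratios for binary outcomes (3.4 at 80% power) does not reproduce under the documented design: power is about 68–73%, and about 51–57% once the planned 6-month exclusion is applied

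*Protocol article*

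**What the plan says.** The Minimum detectable effects section says of the binary outcomes that "it will provide 80% power to detect intervention odds ratios of 3.4 to 6.7, depending on the number of patients included in the analysis (200–300"). It also makes the value depend on "the prevalence of the outcome (20 to 50"%), and the range is given "again after adjusting for a linear temporal trend and confounders". The test level comes from the Cox sentence just before it: "80% power within two-sided tests with alpha of 0.05 to detect a hazard ratio of 2.25". The figures are attributed to simulations whose settings are not shown. The same section says that the sample size rests on feasibility and that effect estimation is a secondary objective.

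The design inputs are in Chart review: two years before and two years after implementation, the six months before implementation left out, and a volume of patients described thus: "there are about 75 patients with head and neck cancer seen in the clinic each year who meet enrollment criteria". That leads to roughly 300 patients over four years. The section on classification of exposure repeats the 6-month exclusion. The Analysis section puts calendar time in every model and names the model: "For binary outcomes including loss to follow-up and completion of treatment steps such as post-treatment radiation within 6 weeks, logistic regression will be used".

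**The concern.** An indicator that switches from 0 to 1 at implementation is strongly correlated with linear calendar time, so adjusting for the trend removes most of the information on the tool's effect. The most favourable combination in the stated range (300 patients, 50% prevalence) should be the one that yields 3.4, and it appears too small an odds ratio for that design.

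This sentence is the only precision statement for completion of tumor board recommendations, which is the primary outcome of the post-treatment cohort, and for loss to follow-up. The Discussion says that the results will inform a multi-center trial. Readers and planners would credit the pilot with more ability to detect effects than it has.

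**Working it through.** **Inputs.** From the article: two-sided alpha 0.05, 80% power, 200–300 patients, prevalence 20–50%, logistic model with a linear time term, two years before and two after, about 75 patients per year, six months excluded. Assumed, because not stated: entry uniform in time, no true trend unless noted, no confounders. Prevalence was tried both as the overall and as the pre-period proportion.

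**1. Is the trend penalty in the printed range?** Yes, at least in part. Without the time term, the OR detectable with 300 patients and 50% prevalence is about 1.9, far below 3.4.

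**2. Information left after trend adjustment, no gap.** Take implementation as time 0. Mean entry time is −1 before and +1 after.
- Between-period variance of time: 0.25 × 2² = 1
- Within-period variance: 2²/12 = 0.333
- R² of exposure on time: 1/1.333 = 0.75
- Residual variance of exposure: 0.25 × (1 − 0.75) = 0.0625

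**3. Ceiling at OR 3.4, 300 patients.** The best case gives every patient outcome probability 0.5.
- SE of the log OR ≥ 1/√(300 × 0.25 × 0.0625) = 0.462
- ln(3.4)/0.462 − 1.96 = 2.65 − 1.96 = 0.69, so power ≤ 75.5%
- Smallest OR at 80% power: exp(2.80 × 0.462) = 3.65

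**4. Realistic values, no gap.** From the Fisher information of the logistic model, with simulation in agreement:

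| Patients, OR | Prevalence | Power | OR at 80% power |
|---|---|---|---|
| 300, 3.4 | 50% overall | 72% (simulated 72–73%) | 3.9 |
| 300, 3.4 | 50% pre-period | 68% (simulated 68–71%) | 4.3 |
| 200, 6.7 | 20% overall | 68% (simulated 69–70%) | 9–10 |
| 200, 6.7 | 20% pre-period, rising | 84% (simulated 86–87%) | below 6.7 |
| 200, 6.7 | 50% pre-period | 80% (simulated 83%) | about 6.7 |

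A true trend running against the effect raises simulated power at OR 3.4 to about 74–75% at most.

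**5. With the 6-month exclusion, still 300 patients.** Entry runs from −2 to −0.5 (share 3/7, mean −1.25) and from 0 to 2 (share 4/7, mean 1).
- Between-period variance: (3/7)(4/7) × 2.25² = 1.240
- Within-period variance: (3/7)(1.5²/12) + (4/7)(2²/12) = 0.271
- R² = 1.240/1.511 = 0.821, so the variance inflation rises from 4 to about 5.6
- Residual variance of exposure: 0.245 × 0.179 = 0.0439
- SE floor: 1/√(300 × 0.25 × 0.0439) = 0.551
- Ceiling: 1.224/0.551 − 1.96 = 0.26, so power ≤ about 60%

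The full calculation gives about 51–57% at OR 3.4 and a detectable OR of about 5.3–7.3. At OR 6.7 with 200 patients it gives about 56–73% across the three prevalence readings tabulated above. At 75 per year the exclusion would also cut the sample to about 3.5 × 75 = 262, which lowers power further.

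**6. Direction for loss to follow-up.** The tool should lower this outcome. If 20% is the pre-period value and it falls with an OR of 1/6.7, power without the gap is about 49% with 200 patients and 66% with 300.

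**7. Two cross-checks.** The Cox figure is consistent with the no-gap design if about 64% of patients have the event (assumed): ln(2.25) × √(300 × 0.64 × 0.0625) − 1.96 = 0.85, or 80.2% power. A one-sided 5% test without the gap gives simulated power of 81.2% at OR 3.4 (300 patients, 50% overall) and 79.8% at OR 6.7 (200 patients, 20% overall).

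**The case against.** The ceiling rests on uniform entry and an even split, and the article shows neither for its simulations. It gives an approximate number of patients seen per year, whereas entry to a cohort is diagnosis or start of treatment. If entry tapered away from implementation on both sides, power at OR 3.4 with 300 patients would be 80–83%. A 1-year/3-year split would give about 83% at 50% overall prevalence. An article may leave such settings to the full plan. This stands as far as it goes: a reader might infer that 80% power is impossible under any entry pattern, and the documents do not support that. But those patterns are not the described design of steady volume over two years on each side, and the 6-month exclusion removes patients closest to implementation, which works against the plan.

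A reader might also infer that the whole range is wrong. It is not shown to be. Without the gap, 6.7 holds if prevalence is the pre-period value and the outcome rises.

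The direction of an OR can be called a coding choice. That holds at 50% prevalence. It does not hold at 20%, because recoding loss as retention turns 20% into 80%, which is outside the stated range.

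The match with a one-sided test might suggest that one was used. It is a lead to check and proves nothing, since the article states two-sided tests.

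Finally, the pilot is sized on feasibility, progression depends on tool use, and what a null result excludes is read from its confidence interval. This limits the consequence but does not make the figure right.

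**Conclusion.** The stated lower end does not reproduce. Under uniform entry, an even two-year/two-year split, a two-sided 5% test and no confounders, power at OR 3.4 with 300 patients and 50% prevalence falls short of 80% by about 7 to 12 points. Even the theoretical ceiling is 4.5 points short. With the planned exclusion the shortfall is about 23 to 29 points. The upper end is unresolved without the exclusion, because prevalence is not defined, and it falls short once the exclusion is applied. Leaving out confounders favours the plan throughout. A reader might take about 3.9 to 9, the no-gap range on the overall-prevalence reading, as the corrected one. It is not, because it ignores the exclusion that the article itself fixes. The point merits correction but changes no sample size, analysis or progression rule.

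**What to change.** Rerun the existing simulation with the two-sided test, the 6-month exclusion, the number of patients left after it, and the planned confounders. Replace 3.4 to 6.7 with the result. State whether prevalence is overall or pre-period, and the entry pattern assumed. Report loss to follow-up as an OR below 1, the direction of benefit. Check in passing which sidedness and calendar layout the existing code used. The cost is one rerun, a revised sentence and a less favourable stated detectable effect. No further patients or data are needed.
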